### Quality control

All researchers will be required to undergo special training classes to guarantee the quality of the study. The training classes will introduce researchers to the trial’s details. For example, researchers will be trained to use the central randomized system, to fully understand the inclusion and exclusion criteria, and to fill in the CRFs. Additionally, clinical monitors will also check the trial processes and CRFs. Patient drop-outs and their reasons will be fully recorded.

### Ethics and dissemination

Medical Ethics Committees at Tianjin University of Traditional Chinese Medicine has approved this protocol (approval number is TJUTCM-EC20140006 and). Patients’ data will be stored securely and the results of the present study will be published in a peer-reviewed journal.

## Discussion

This study protocol expands current literature regarding the efficacy of acupuncture on CINV. Previous reviews showed that acupoint stimulation has a certain effect on CINV. However, the effects of different acupoint combinations are inconsistent. We designed our trial to compare the effects of distal-proximal point association and local distribution point association.

More than 300 acupuncture points are located on the body and each point has its own therapeutic indication. The correct selection and combination of acupoints are the keys to the curative effects of acupuncture [6]. Before developing the trial protocol, we screened a range of published articles and ancient books. Our literature search showed that PC6, ST36, and CV12 are the most commonly used acupoints for managing CINV [16, 17]. We selected PC6 and ST36 as the distal acupoints, and CV12 as the local acupoint. Based on the theory of Chinese acupuncture, distal-proximal acupoint association and local distribution point association are the two classic methods for combining acupoints. Distal-proximal acupoint association is also the most commonly used method in clinical applications. In this trial, there are three different acupuncture groups: “PC6 and CV12” and “ST36 and CV12” are the two disal-proximal acupoint association groups, and “CV12 and CV13” is the local distribution point association group. Therefore, we expect that distal-proximal point association (“PC6 and CV12” or “ST36 and CV12”) will have better effect than local distribution point association (“CV12 and CV13”). Furthermore, we can screen the most effective acupoint combination for clinical application from these three groups.

Although the manipulators and participants cannot be blinded to the group allocation in this study, all outcome measures will be administered and collected by a blinded estimator, and statisticians blinded to group assignment will perform data analysis. With respect to clinical quality control, the manipulators, estimators and statisticians will work independently to reduce the adverse impacts of artificial factors on data. A third party has been invited to manage data independently and to design a central randomization system for minimizing bias and enhancing clinical research quality.

In conclusion, the results of this trial are expected to assess the clinical efficacy and safety of distal-proximal point association and the local distribution point association by electro-acupuncture in the management of CINV.

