### Design

This is a four-armed parallel randomized controlled trial (RCT). 240 participants will be randomly assigned to four groups (a control group and three acupuncture groups) through central randomization in a 1:1:1:1 ratio. The flow chart is shown in Fig. 1.

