### Sample size calculation

A sample size calculation was performed based on the result of a trial by Shen J [8] and the results of a pilot study. To detect a significant difference between any two groups with a power of 90 % and type I error of 5 %, the calculated number of patients is 192. Considering a 20 % drop-out rate, the total sample size needs 240 patients and 60 patients in each group.

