### Statistical analysis

Statistical analysis will also be performed by the Clinical Evaluation Center at China Academy of Chinese Medical Science. The statistician is blinded from the allocation of groups. The Kruskal-Wallis test will be employed in the analysis of skewed distribution data. Chi-square analysis will be used for categorical variables, and Analysis of variance (ANOVA) for numerical variables. Repeated measures analysis will be used in the different time point assessment. A *P* value less than 0.05 is regarded as statistically significant.

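### The aim of picking the most effective of three acupoint combinations does not match the stated four-group tests and flat 5% threshold

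*Protocol article*

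**What the plan says.** Three parts of the protocol article bear on this point.

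- **Aim.** The Background proposes the trial in order to find the optimal acupoint combination. The Discussion returns to this after stating the expectation that the distal-proximal groups will do better than the local group: "we can screen the most effective acupoint combination for clinical application from these three groups".
- **Analysis.** Under Statistical analysis, "The Kruskal-Wallis test will be employed in the analysis of skewed distribution data", chi-square is named for categorical variables, and "Analysis of variance (ANOVA) for numerical variables". Repeated measures analysis is named for the time points. Significance is P below 0.05 throughout.
- **Size.** Allocation is "through central randomization in a 1:1:1:1 ratio". Under Sample size calculation the target is "To detect a significant difference between any two groups" with 90% power and 5% type I error, and "the calculated number of patients is 192". Allowing for 20% drop-out gives 240, or 60 per group. No effect size, SD or endpoint is given, and no adjustment of the 5% is mentioned.

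**The concern.** Choosing one of three active combinations is a question about differences among those three. In a four-arm trial, ANOVA, Kruskal-Wallis and chi-square each ask whether all four groups are alike. One of the four is antiemetic alone, so the test can be significant because control is worse while the three combinations are the same.

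If the named tests are followed by pairwise tests at the same 5%, the threshold no longer limits false differences among the combinations to 5%. In either case one arm will be numerically on top, and nothing in the stated threshold says when that ranking is strong enough to support a choice.

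At stake is a recommendation for practice. One combination could be put forward over others that are equally good, with an estimate that is on average too favourable.

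**Working it through.** **Inputs from the article:** four equal arms; 192 evaluable, so 192/4 = 48 per arm; 90% power; 5% type I error; 20% drop-out.

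**Assumptions:** two-sided test, normal outcome with SD 1, and 192 derived from an unadjusted comparison of two means. The selection results come from 200,000 simulated trials with 48 per arm.

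**1. The article's own figure.** 192/(1 − 0.20) = 240, which agrees. The 192 cannot be reproduced without an effect size.

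**2. Implied effect.** d = (1.960 + 1.282) × √(2/48) = 3.242 × 0.2041 = 0.66 SD. Had a Bonferroni adjustment over three pairs already been built in, it would be (2.394 + 1.282) × 0.2041 = 0.75 SD.

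**3. What a significant four-group test shows.** Let the three combinations be equal, each 0.66 SD better than control. The non-centrality is 48 × 0.75 × 0.662² = 15.8 on 3 and 188 degrees of freedom, and power is 92.5%. These rejections are correct, because control does differ. They carry no information on which combination is best.

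**4. Unadjusted pairwise tests at 5% with no true differences.** At least one false difference occurs in 12.2% of trials over the three acupuncture pairs and in 20.3% over all six pairs. A prior four-group test gives the three acupuncture pairs little protection when control is worse, since it is then passed in most trials.

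**5. Picking the top-ranked combination.** The best arm is set 0.66 SD better than control.

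| True lead over both other combinations (SD) | Top-ranked arm is truly best | Four-group test significant and top arm separated from both others (unadjusted 5%) | Mean overstatement of top arm's effect against control (SD) |
|---|---|---|---|
| 0 | no best arm exists | 1.4% | 0.12 |
| 0.1 | 54% | 2.4% | 0.11 |
| 0.2 | 74% | 6.5% | 0.08 |
| 0.33 | 91% | 21% | 0.04 |
| 0.66 | over 99% | 82% | about 0 |

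The value 0.12 agrees with theory: 0.846/√48 = 0.122, which is 0.122/0.662 = 18% of the implied effect. With all 60 per arm evaluable it would be 0.846/√60 = 0.109.

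**6. Price of adjustment at 0.66 SD, by Bonferroni.**

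- Three acupuncture pairs: 3.242 − 2.394 = 0.848, power 80%.
- All six pairs: 3.242 − 2.638 = 0.604, power 73%.
- To restore 90% over three pairs: 48 × (3.676/3.242)² = 61.7, so 62 per arm. That is 248 evaluable and 248/0.80 = 310 randomised.

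**The case against.** The strongest reply is that the article condenses a fuller plan. It names families of tests and does not exclude follow-up comparisons, and the sample size sentence shows that pairwise comparison is intended. A post-hoc procedure may be in the full protocol or analysis plan. The selection sentence is also a Discussion remark without a decision rule, and the listed Objectives do not mention choosing a best arm.

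Much of this stands, and it rules out three stronger readings that a reader might infer.

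- **That the trial cannot identify a best combination.** The documents do not support this. It is true of the four-group tests taken alone, but pairwise comparison is evidently meant.
- **That a non-existent winner would be named in about 92% of trials when the three are equal.** That figure is the rate of a correct rejection. Naming a winner needs a further step, which the article does not prescribe. If even an unadjusted separation from the runner-up is required, a false winner appears in about 1.4% of such trials. The 12% likewise counts any false difference among the three, not false winners.
- **That the chosen arm's benefit will be overstated.** This is an average tendency, largest with equal arms and about nil with a clear leader. A single trial's estimate can also be too low.

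The reply does not remove what the article does state. Finding the optimal combination is the reason given for the trial, and the only error level stated is 5%, both for sizing any two groups and for declaring significance. Applied pairwise as written, that gives the 12% and 20% above.

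**Conclusion.** The concern holds as a mismatch between the stated aim and the stated analysis. The four-group tests do not rank the combinations, and the 5% threshold applied pairwise allows about 12% false differences among three equal combinations (about 20% over all six pairs).

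Ranking by the observed mean is unreliable for small leads: the top arm is right in 54% of trials at 0.1 SD and 74% at 0.2 SD. The average overstatement of its effect is at most about 0.12 SD. The design separates a winner from both rivals with fair probability (82%, unadjusted) only if the lead is about 0.66 SD.

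These figures assume a normal outcome and 48 evaluable per arm. The primary outcomes are episode counts, toxicity grades and Likert items, so the SD-scale figures are a guide only. The 0.66 SD is back-calculated and is not a figure from the article. The point is worth correcting because the stated purpose is a choice for clinical application.

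**What to change.** State in the analysis section that a combination will be called most effective only if it is separated from both other acupuncture groups in multiplicity-adjusted comparisons among the three. Tukey's method or Hsu's comparisons with the best would serve, with a rank-based equivalent for skewed counts. Otherwise, report the combinations that cannot be distinguished from the best and describe any ranking as exploratory. The separation rule guards against a false winner. The adjustment keeps the individual pairwise claims, such as distal-proximal over local, at the stated error level.

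No new data are needed, and recruitment was still under way when the article was written. The cost is power: about 80% instead of 90% for each acupuncture pair at 0.66 SD by Bonferroni. The stated 90% should therefore be described as unadjusted, if that is how it was derived. Separation from both rivals is harder to achieve than any single pairwise difference, so the trial may have to report no single best combination. Keeping 90% per pair would take about 310 patients, which is a separate decision. A selection-adjusted estimate beside the raw one is optional.

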## Trial status

The first participant was recruited on 26 June 2015. This study is currently recruiting participants.

## Abbreviations

ALT: Glutamic-pyruvic transaminase
ANOVA: Analysis of Variance
AST: Glutamic oxalacetic transaminase
BUN: Blood urea nitrogen
CINV: Chemotherapy- induced nausea and vomiting
Cr: Urine creatinine
CRF: Case Report Form
CV12: The acupoint of Zhongwan
CV13: The acupoint of Shangwan
FACT-G: The Functional Assessment of Cancer Therapy - General
KPS: The scoring of Karnofsky
LI4: The acupoint of Hegu
PC6: The acupoint of Neiguan
RCT: Randomized Controlled trial
ST36: The acupoint of Zusanli
STRICTA: Standards for Reporting Interventions in Clinical Trials of Acupuncture
TBIL: Total bilirubin
TCM: Traditional Chinese Medicine
